
### Sample size

We expect higher rates of treatment success in the intervention arm receiving integrated treatment compared to the standard arm. The power calculation is based on the following assumptions:
The power is set at 90% with a two-sided alpha (α) error of 5%.Comparison of SVR at 12 weeks.Up to 33% lost to follow-up at 12 weeks after treatment.Equal proportions between the groups, 30% higher rates of successfully cured in integrated compared to standard treatment (e.g. 50% in the standard arm and 80% in the intervention arm).Statistical power calculations in Stata.

Based on these assumptions, 87 persons are required in intervention arm and 87 persons in the control arm. Reducing the differences in rates of successfully cured to 25% while reducing power to 80%, 99 persons in each arm would be required (or 66 persons if assuming no lost-to-follow-up).

### Recruitment

All PWID receiving OAT treatment or low-threshold care from included clinics will be considered the reference target population. As part of an annual clinical assessment, patients will be informed about the study and asked for consent to participation. All patients in target population will be offered annual clinical assessment and study participation. For those giving informed consent, an extended clinical assessment will be offered and those diagnosed with chronic HCV will be randomised for the intervention.

### Allocation and blinding

We will use block randomisation with a 1:1 ratio using blocks of 10 to ensure relatively similar distribution between both arms throughout different time periods of the trial. Randomisation will be electronically registered. The randomisation will be stratified by site/county (site 1: Bergen/Hordaland and site 2: Stavanger/ Rogaland).

Even though complete blinding is regarded as difficult and would probably come at a cost of reduction in external validity [21], there will be some degree of blinding/masking. Randomisation will be disclosed to physician and other health care staff providing treatment and follow-up for PWID, but not to research nurses conducting data collection for outcomes. Patients will be informed of which intervention arm they are randomised to and the form of follow-up they will receive, but not on other follow-up alternatives they do not receive and what the hypotheses for the study are.

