### Data collection and management

Data collection and follow-up will be given in line with Table 1 and Fig. 1.

**Table 1 Tab1:** Flow chart of the study outlining follow-up visits and assessments at each visit

	Screening 1 (part 1)	Screening 2 (part 2)	Treatment initiation or referral to standard treatment (physician)	Treatment follow-up (4 weeks after initiation)	Treatment follow-up (8 weeks after initiation)	Treatment follow-up (12 weeks after initiation)	Effect assessment (12 weeks after completion)	Annual follow-up
Acceptable time shift (days)				± 7	± 7	± 7	± 14	± 60
Physician assessment			X				X	X
Research nurse assessment	X	X					X	X
- Informed consent	X							
- Eligibility assessment	X	X	X					
- Follow-up by staff delivering treatment and providing information (several times weekly)			X	X	X	X		
- Clinical assessment	X	X	^b^	^b^	^b^	^b^		X
- Counselling on prevention			X	X	X	X	X	X
Elastography^a^		X					(X)	X
Lab tests								
- Viral testing	X						X	X
Full blood count and transaminases	X			^b^	^b^	^b^	X	X
HSCL-10 (mental health)	X						X	X
FAS (fatigue symptoms)	X						X	X
EQ-5D-5 L (quality of life)	X						X	X
Infection risk behaviour	X						X	X
Substance use patterns	X						X	X
HCV genotyping and viral load	X						X	X

^**a**^Elastography after treatment will be assessed in Bergen and not in Stavanger due to elastography availability only in hospital clinic and not outpatient clinic

^b^Additional tests will be taken on clinical indication

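### A single published block size of 10 per site, with arms disclosed to treating staff, lets up to about one assignment in six be deduced by anyone who sees the whole site sequence

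*Protocol article*

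**What the plan says.** Under Allocation and blinding, the article fixes one block size at a 1:1 ratio: "We will use block randomisation with a 1:1 ratio using blocks of 10 to ensure relatively similar distribution between both arms". The stated reason is to keep the arms similar in number over the course of the trial. There is one stratification factor with two levels: "The randomisation will be stratified by site/county". Each site therefore runs one sequence of blocks, five patients per arm in each.

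The same section says who learns the arms. Treating staff do: "Randomisation will be disclosed to physician and other health care staff providing treatment and follow-up for PWID". It makes an exception for the nurses who gather outcome data, since the allocation is disclosed to staff "but not to research nurses conducting data collection for outcomes". The arm is also known to the patient: "Patients will be informed of which intervention arm they are randomised to". On the mechanics it says only that randomisation is registered electronically. The abstract describes the trial as ongoing, so the block size became public during the trial.

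In Table 1, informed consent and the first two eligibility checks fall in the two screening visits, which are marked for the research nurse and not for the physician. The eligibility row reads "Eligibility assessment X X X"; its third mark is at the physician visit for treatment initiation or referral. Under Study settings and participants, Bergen has an OAT clinic in each district and Stavanger also has more than one clinic.

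**The concern.** In a block of 10 with five per arm, once one arm has been used five times the rest of the block is determined. Electronic registration can hide the list, but it cannot stop someone who knows the block size and the past assignments from counting. Here the block size is published, and past assignments are disclosed to physicians and other staff who take part in assessing patients.

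Both primary outcomes, SVR and time to treatment initiation, depend on how well a patient attends and engages. If someone with influence over whether or when a patient enters could foresee the arm, patients expected to struggle with hospital referral could be brought forward, held back or discouraged. Such selection acts before randomisation, so analysing patients as randomised does not remove it. The Discussion relies on individual randomisation to limit confounding.

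**Working it through.** **Inputs.** Block size 10, ratio 1:1, two site strata (Allocation and blinding). Totals: 87 per arm (Sample size) and about 200 (abstract).

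**The plan's own total.** With 50% against 80%, 90% power and two-sided 5%, the continuity-corrected formula gives 58 per arm. Then 58/(1 − 0.33) = 86.6, rounded up to 87, so 2 × 87 = 174. The stated figure is reproduced, and this point does not affect it.

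**Ceiling for a full observer.** Position k is forced when all remaining places in the block belong to one arm. By position:
- position 10: 1
- position 9: 4/9 = 0.444
- position 8: 4/9 × 3/8 = 0.167
- position 7: 0.167 × 2/7 = 0.048
- position 6: 0.048 × 1/6 = 0.008
- positions 1 to 5: 0

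The sum is 1.67 per block, which agrees with 2m/(m + 1) = 10/6 for m = 5 and with enumeration of all 252 orderings. The share is 1/6 = 16.7%: 174/6 = 29 patients, or 200/6 = 33. Every block has at least one forced assignment.

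Always guessing the arm that is behind is right on average in m + 2^(2m−1)/C(2m, m) − 1/2 = 5 + 512/252 − 0.5 = 6.53 of 10 assignments. That is 65.3%, against 50% by chance.

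**Partly informed observer.** Suppose someone sees each assignment at the site independently with probability p and still knows the block starts. Certainty requires that one arm is used up and that all five of its assignments were seen, so the share is p⁵/6. The documents do not give the number of clinics, so p is an assumption.

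| p | share known with certainty |
|---|---|
| 1.00 | 16.7% |
| 0.75 | 0.237/6 = 4.0% |
| 0.50 | 0.031/6 = 0.5% |
| 0.25 | 0.001/6 = 0.02% |

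Simulation agrees (3.9%, 0.5% and 0.02% for the last three rows).

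**Effect of varying the block size.** Simulated for an observer who sees the whole site sequence and even knows the set of possible sizes, but not which size is in use:

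| sizes | known with certainty | best guess correct |
|---|---|---|
| 10 (fixed) | 16.7% | 65% |
| 4, 6, 8 | 2.3% | 68% |
| 6, 8, 10 | 1.5–1.6% | 66–67% |
| 6, 8, 10, 12, 14 | 0.4–0.6% | 65% |

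Varying the size nearly removes certainty. It does not reduce the success of guessing.

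**The case against.** A reader might infer that about one in six assignments is in practice known to clinic staff and that enrolment is being steered by arm. The documents support neither.

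- **Who sees the sequence.** Several clinics draw on each site list. Staff who see only their own clinic's patients know almost nothing for certain, as the p⁵/6 table shows. This stands, so 16.7% can be quoted only as a ceiling.
- **Who controls entry.** Table 1 places consent and the first two eligibility checks with research nurses, and nurses who collect outcomes are not told allocations. If these are the same nurses, the people admitting patients are not given the information needed for counting. This stands with that condition, which the article does not settle.
- **The physician's eligibility check.** It sits in a column already headed by initiation or referral, and Table 1 does not show when randomisation occurs. If randomisation comes first, this check cannot influence entry. The timing is open, so the check cannot be treated as a proven route.
- **Limited discretion.** Under Recruitment, all patients in the target population are offered participation, and consenting patients with chronic HCV are randomised. The eligibility criteria are largely objective. This lowers the risk, but the timing of a patient's assessment may still be open to influence.
- **Ten is a fairly large block.** Fixed blocks of 4 would give 1/3 forced and blocks of 6 would give 1/4. True, but the size is still single and published.
- **The full protocol may describe concealment.** It may, and its absence from an article is not criticised here. Concealing the list does not prevent deduction from a stated block size and known past assignments.

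**Conclusion.** The point holds as a design weakness that should be changed while blocks remain unopened. The stated rule makes up to 1.67 of every 10 assignments deducible in advance, at most about 29 of 174 or 33 of 200 patients. That figure assumes an observer with the whole site sequence and the block starts. Under the assumed partial views it is about 4% at 75% seen and 0.5% at 50% seen.

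This is a risk of selection before randomisation. The article does not show that anyone who decides on entry has the necessary view, nor that selection has occurred. The aim given for blocks of 10, similar arm sizes over time, does not need one fixed, published size.

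**What to change.** For blocks not yet opened, amend the clause under Allocation and blinding that fixes the block size at 10. It should say that block sizes vary at random within site and are not disclosed to clinic staff or research nurses; the actual sizes should be kept out of documents they can read. For a full observer this cuts assignments known with certainty from 16.7% to roughly 0.5–2%. The guess rate stays at about 65% or slightly higher, so the change should not be presented as ending predictability.

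The cost is a settings change in the electronic system and one amended sentence, with no extra patients. The largest possible imbalance per site is half the largest block: 7 with sizes up to 14, or 5, as now, with sizes up to 10. Enrolment began in May 2017 and the article does not say how many blocks remain, so the prospective benefit cannot be sized.

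A big-stick rule with limit 5 is an alternative with a different trade-off, not a clear improvement. Its guess rate is about 54.6%. Since that rate equals 0.5 + f/2, about f = 9% of assignments stay forced for a full observer who knows the rule.

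For patients already randomised under fixed blocks, compare baseline prognostic factors by arm in late block positions (6 to 10, where forced assignments can occur, and most of all 9 and 10) with positions 1 to 5, where none can. Report it descriptively, because at most about 33 forced assignments are expected. It needs no new data beyond the allocation list.

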### Interventions

Participants randomised to standard care are first assessed and diagnosed at the integrated care clinics for PWID by nurse and physician and when found in need of treatment, are referred to a hospital clinic for further assessment and treatment. The standard care generally involves being referred to the medical outpatient clinic. The clinic will send a letter informing on time of appointment usually some weeks later and could involve some additional blood samples and imaging before initiating DAA treatment. Subsequently, an electronic prescription is given in a consultation where treatment is initiated. The medications given are in principle equivalent in the two trial arms. Most will receive medication combinations of either elbasvir/grazoprevir 50/100 mg or sofosbuvir/ledipasvir 400/90 mg (for genotype 1 and 4) or sofosbuvir/velpatasvir 400/100 mg (for genotype 2 and 3) – sometimes also in combination with voxilaprevir 100 mg or ribavirin 200 mg due to specific clinical indications. Glecaprevir/pibrentasvir 100/40 mg may also be used in special cases. Patients are generally given follow-up consultations every 4 weeks during treatment and a post-treatment assessment 12 weeks after completed treatment. Typically, this involves a total of 4–5 consultation visits at the hospital.

Participants randomised to integrated treatment are given integrated assessment and treatment at the clinics for PWID (by nurse and physician). For those found to be in need of treatment, medications are made available by a nurse that gives follow-up for OAT or low-threshold care for PWID. Follow-up during treatment is given in parallel with delivery of OAT treatment and other care. At 12 weeks post treatment, a research nurse takes blood samples to assess the treatment effect.

The differences between the delivery platforms in the two trial arms involve the following main aspects:

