Treatment adherence assessed by proportion of doses observed being taken in intervention group and reported obtainment from pharmacies of the prescribed drugs combined with self-reported questions on adherence collected at 4, 8 (and 12 for treatment recommended beyond 8 weeks) weeks after treatment initiation. The self-reported questions categorise adherence during last four weeks into rarely, sometimes but less than half of the doses, between 50 and 80% of the doses, more than 80% of the doses, and always (95% of doses or more). These outcome measures will be collected at the OAT/PWID clinicsReinfection will be defined as HCV RNA recurrence following SVR. Incidence rates will be calculated using person-time techniques assuming a Poisson distribution. All patients achieving SVR will be assessed for reinfection 3 months after treatment and then annually. HCV RNA positive samples will be further analysed with a quantitative HCV RNA count, HCV genotyping. Relapse is defined as presence of the same virus strain at the time of diagnosis and at the end of treatment. Anti-HIV and use of other drugs will also be assessedChanges in quality of life will be assessed with the questionnaire EQ-5D-5 L (https://euroqol.org/eq-5d-instruments/) in addition to a self-reported question on happiness on a 0 to 10 scale at 12 weeks after treatment compared to before treatmentChanges in fatigue will be assessed with the Fatigue Symptom Scale at 12 weeks after treatment compared to before treatmentChanges in psychological well-being will be assessed with the Norwegian validated translation version of Hopkins Symptom Checklist (SCL-10) at 12 weeks after treatment compared to before treatmentAssessment of changes in substance use will be assessed with self-reported use of the following drug categories the last 30 days, the last 12 months and ever: Alcohol, tobacco, cannabis, amphetamines, cocaine, heroin, other opioids not prescribed by physician, benzodiazepines or z-hypnotics, hallucinogens, solvents and gamma hydroxybutyrate (GHB), anabolic steroids and other drugs at 12 weeks after treatment compared to before treatmentAssessment of changes in injecting risk behaviour will be performed with questions assessing sharing of needles and other user equipment before and after HCV treatment at 12 weeks after treatment compared to before treatmentHealth provider costs by using an ingredients approach, where quantities used and the value (or price) of each unit is estimated in the both trial arms. Health care costs will be used in a health economic evaluation, where both costs per cured patient and per Quality Adjusted Life Year (QALY) gained will be estimated.

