**Fig. 1 Fig1:**
[figure not shown]
Overview of follow-up for the study * The arrows are indications of when the various measured are timed

The blood samples for the primary outcome measures will be collected at the OAT/PWID clinics for participants randomised to integrated care and at the hospital outpatient clinic for the participants randomised to standard care. However, for patients who do not come for assessment at the hospital clinic 12 weeks after treatment, efforts will be made to collect these blood samples at the OAT/PWID clinic. For the remaining outcome measures, these will be measured at the OAT/PWID clinics by research nurses through a structured interview for both participants randomised to standard and integrated treatment.

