Our trial involves some limitations and several strengths. For the trial it is difficult to ensure complete blinding, however, we will aim for blinding of data collectors and some degree of blinding for participants. The study is also funded from public sources ensuring independency. We also have a biological primary outcome. Thus, substantial information biases are considered unlikely. The study is individually randomised minimizing potential confounding. The study population of PWID will include a large proportion struggling to obtain standard care. This will not be applicable to all groups of people with substance use disorders. For people with substance use disorders with higher levels of functioning and less need for regular treatment follow-up, the need for treatment integration might not be as relevant. The study setting is also very suitable to test out treatment integration. The time prior to change in the national guidelines for treatment of HCV made it necessary for some people to delay HCV treatment initiation. This might impact negatively on the treatment outcomes, but probably is balanced between the arms. Further, most of the participants will be treated after the guideline changes where treatment is now available independent of stage of liver fibrosis. Subsequently, we assume that this effect will not be substantial. The study might be well suited to assess some biological effects of HCV infection such as to which extent HCV contributes to fatigue, reduced quality of life, occurrence of mental disorders and continued drug use. The study size should be sufficient to answer the primary objectives with high precision and is assumed to have adequate precision also for secondary objectives. In terms of safety, the frequent follow-up of PWID could improve detection of potential adverse effects of the applied medications. One can see trials on a continuity from efficacy trials optimising internal validity through homogeneous population to effectiveness trials optimising external validity with a more heterogeneous population. This trial is tending towards the effectiveness side of the spectrum. An alternative design could have been a stepped-wedge trial which could have required slightly smaller sample sizes and would also be well opted to measure effectiveness of integrated treatment. However, we expect to have enough participants to meet the sample size requirements. On the other side, stepped-wedged trials generally take longer time to conduct due to the time delay. In addition, our more conventional trial design is less vulnerable to confounding from time trends.

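### The article says research nurses who collect outcomes are not told the allocation, but its 12-week sampling arrangement signals most patients' arm to that same role

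*Protocol article*

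**What the plan says.** All references are to the protocol article.

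- **Allocation and blinding** promises only partial masking ("there will be some degree of blinding/masking") but is specific about one group. Treating physicians and staff learn the allocation, "but not to research nurses conducting data collection for outcomes". The same section says: "Patients will be informed of which intervention arm they are randomised to and the form of follow-up they will receive".
- **Interventions**, in the paragraph on the integrated arm only: "At 12 weeks post treatment, a research nurse takes blood samples to assess the treatment effect".
- **Data collection and management** (text under Fig. 1) says the blood samples for the primary outcome are "collected at the OAT/PWID clinics for participants randomised to integrated care and at the hospital outpatient clinic for the participants randomised to standard care". If a patient does not attend the hospital, staff try to obtain the sample at the OAT/PWID clinic. Research nurses obtain all other outcomes by structured interview at the OAT/PWID clinics, in both arms.
- **Table 1** puts viral testing, the research nurse assessment and the questionnaires in one column, the effect assessment 12 weeks after completion. It shows no research nurse assessment at the visits 4, 8 and 12 weeks after initiation.
- **Outcomes** defines adherence partly by "proportion of doses observed being taken in intervention group and reported obtainment from pharmacies of the prescribed drugs", combined with self-report at those on-treatment time points.
- **Discussion** says "we will aim for blinding of data collectors". It then cites public funding and a biological primary outcome, and concludes that material information bias is improbable.

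**The concern.** Withholding the allocation from an assessor helps only if the assessor's other tasks do not reveal it. Here the same staff role that is to be kept unaware has a task at the outcome visit that depends on the arm.

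The outcomes at stake are those elicited face to face: quality of life, fatigue, psychological distress, drug use and sharing of injecting equipment. Answers on the last two are socially sensitive and can be influenced by how questions are put and probed. If the interviewer knows the arm, a difference in change between arms could partly reflect the interview. A reader who relies on the blinding statement and on the Discussion's conclusion would not expect this.

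**Working it through.** No arithmetic applies, and the article gives no figure to reproduce. The check sets the sections side by side.

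1. **Same role.** Allocation and blinding names research nurses as the outcome collectors kept unaware. Interventions gives the 12-week integrated-arm sample to a research nurse. Data collection and management gives the interviews in both arms to research nurses.
2. **Same occasion.** Table 1 places viral testing, the research nurse assessment and the questionnaires at the same effect assessment.
3. **What the nurse can infer at the OAT/PWID clinic.**

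| Situation at the 12-week visit | Arm it points to |
|---|---|
| Sample due as planned | Integrated |
| No sample due because it is taken at the hospital | Standard |
| Catch-up sample after a missed hospital visit | Standard |

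The third row is the article's own exception. It stops the place of sampling from being a perfect marker, because a sample drawn at the clinic may come from either arm. But a nurse who knows that it is a catch-up sample also knows that a hospital visit had been planned.

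4. **Second route.** Patients know their arm and form of follow-up. The article describes no step to keep them from mentioning it in the interview.
5. **Outcomes exposed.** Outcomes lists eight secondary measures: adherence, reinfection, quality of life, fatigue, psychological well-being, substance use, injecting risk and provider costs. Five of them (quality of life, fatigue, psychological well-being, substance use, injecting risk) are questionnaire or interview measures at the effect assessment. Reinfection rests on HCV RNA, and costs on resource quantities and prices.
6. **Adherence.** Data collection and management, read literally, gives adherence to research nurses as one of the remaining outcomes. Table 1 shows no research nurse at the on-treatment visits when self-reported adherence is due; the follow-up marked there is by the staff delivering treatment, who know the allocation. The two places do not agree on who collects it.
7. **SVR.** HCV RNA is read in a laboratory, so the interviewer's knowledge of the arm has little way to alter it.

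**The case against.** The strongest reply has five parts.

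- *The article claims only partial blinding, and the Discussion lists incomplete blinding as a limitation.* This stands against any inference that blinding is claimed in full or is wholly absent. It does not answer the specific sentence about research nurses, which is the one the procedures undercut.
- *The article does not say that the nurse who draws blood is the interviewer, or that blood is drawn first; such details belong to a full protocol.* This is fair, and a full protocol may already separate the tasks. As written, however, one role has both tasks at one visit.
- *Structured interviews and standard questionnaires limit interviewer influence.* They reduce it but do not remove it.
- *Adherence does not force unblinding.* A reader might infer that research nurses must know the arm to record adherence. The documents do not establish this: Table 1 puts no research nurse at those visits, and the definition names pharmacy collection alongside observed doses without confining it to the standard arm. What remains is the disagreement over who collects adherence.
- *No inflation of false-positive findings can be derived.* A reader might assume an interviewer shift and calculate one. For example, with 66 assessed per arm the standard error of a standardised difference is √(2/66) = 0.174, and an assumed shift of 0.2 SD would raise a 5% two-sided error rate to about 21%. Nothing in the article supports that shift or its direction. Objectives also states a between-arm comparison only for adherence, and describes quality of life, fatigue and well-being as changes from before to after treatment. The figure is therefore no measure of this problem.

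**Conclusion.** The point holds in a limited form. The statement that allocation is not disclosed to outcome-collecting research nurses conflicts with the sampling arrangement, which signals most patients' arm, though not with certainty every patient's, to that role. Five of eight secondary outcomes are exposed. Bias matters chiefly where their changes are compared between arms. Its size and direction cannot be quantified from the document, and SVR is largely unaffected.

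This rests on two assumptions: that the research nurses who sample and those who interview are the same people or share information, and that the interviewer knows whether a sample is due. Table 1 and the use of one role name make both plausible but do not prove them. The Discussion's reassurance about information bias is sound for the virological outcome and too broad for the interview outcomes.

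**What to change.** 1. Reconcile Interventions, Allocation and blinding, and Data collection and management: have OAT/PWID clinic staff who already know the allocation draw the integrated-arm sample and any catch-up sample.
2. Have research nurses complete and lock the questionnaires before any sampling and before treatment records are opened.
3. Ask patients not to reveal their arm, and have the nurse record a guess of the arm after the interview. Disclosure cannot be ruled out, but the guess shows how well masking held.
4. In the Discussion, limit the statement on information bias to the virological outcome, and describe the interview outcomes as at most partially blinded.
5. Reconcile Data collection and management with Table 1 on who collects adherence data.

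The cost is slightly more work for clinic nurses, a fixed order within the visit and one extra form field. No extra staff are needed. If the visit can no longer be changed, the text corrections and the recorded guess remain feasible.
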